### Termination criteria

This trial will be terminated under the following criteria: (1) clustered serious adverse events are related to intervention measurement with supportive evidence; (2) the administration requested that this trial be discontinued.

### Data management

The original data included ICF, CaseReport Form (CRF), record form of distribution and withdrawal of drug, medication administration monitoring form and medication self-assessment form.

Paper CRF will be used to record data, and EpiData software (version 3.1) will be used for data management. Developing a data verification plan to set up logic verification. Consistency testing will be carried out through double data entry, and the inconsistent results will be checked and corrected against CRF item by item until they are completely consistent. The data administrator will screen the questions according to the manual verification plan in the data verification plan.

Finally, the electronic database will be locked after the project leader, data analyst and data administrator sign the database locking record, then will be submitted to the data analyst.

### Data analysis

The statistical analysis will be conducted by the third-party statistician from the Sichuan Province Evidence-based Medicine Center of TCM using Stata software (version 16.0). The statistical analysis plan is completed and confirmed before the start of trial.

The Full Analysis Set (FAS) includes participants who have been randomized to receive the drugs at least once. Missing data will be used the last observation carried forward (LOCF) method. The Per-protocol set (PPS) includes participants who follow the protocol to implement the inclusion and exclusion criteria and interventions, and complete all the visit plans. It does not include participants who drop-off, lost to follow-up, and discontinue medication for any reason. Only participant with an effective medication rate between 80 and 120% can be included in PPS analysis. The safety set (SS) includes participants who have been randomized to receive the drugs at least once and have experienced AE.

The descriptive statistics of enumeration data will be presented as frequency and percentage. Normally distributed variables will be presented as mean and standard deviation, and non-normally distributed variables will expressed by median and interquartile range. Difference between groups will be assessed with t-test, analysis of variance (ANOVA), rank sum test, and chi-square (χ2) test. Survival analysis will be used for comparison of endpoint outcome between groups, and Kaplan–Meier curve will be used to explore each possible relevant factor. The cox multiple regression model will be used to detect the influence of prognostic factors on endpoint outcome if the amount of data allows. AE will be analyzed and described in detail, and the χ2 test will be used to compare the differences between groups if necessary. The statistical significance is defined as *p* ≤ 0.05.

Subgroup analysis will be based on HbA1c. Level of HbA1c will be stratified into ≥ 8.0% and < 8.0% to evaluate correlation between glycemic control of diabetic patients with macroangiopathy and outcome indicators [37].

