#### Outcome measurement

Changes of the following outcomes from baseline (week 0) to endpoint (week 12) of intervention will be evaluated.

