### Sample size

This is a randomized, double-blind, placebo-controlled superiority trial. The primary outcome indicator, CIMT, is used as the basis for sample size estimation. The mean of CIMT of the placebo group is 1.12 mm [40–42]. In this trial, the mean of CIMT of the treatment group is estimated at 1.03 mm, and the standard deviation of two groups is 0.10. The superiority margin is 0.03 (one-sided test, α = 0.025, 1-β = 0.8). The sample allocation ratio between the two groups is 1:1. Using PASS 15 software, the minimum sample size is calculated to be 90. In addition, considering the dropout rate of 20%, we plan to enroll a total of 114 participants.

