### Drop-out criteria

Participants who have intolerable adverse reaction and withdraw voluntarily during the trial.The ratio of ALT to AST of participants is 3 times higher than the upper limit of normal value of that, and it is still abnormal after review within a week.Creatinine of participants is 1.5 times higher than the upper limit of normal value of that, and it is still abnormal after review within a week.Participants who fail to take the drugs as required or have incomplete data.Participants violate the protocol to change or add drugs that are not within the prescribed scope and affect the assessment of efficacy.Participants who are lost to follow-up without explanation.Participant who is unblinding.

They will be required to return for the last observation as much as possible, and the relevant data will be included in the datasets.

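### LOCF is fixed for the full analysis set although CIMT is compared only at weeks 0 and 12, and the sample size does not allow for the zero changes this can create

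*Protocol article*

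**What the plan says.** All places are in the protocol article.

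- **Data analysis:** "Missing data will be used the last observation carried forward (LOCF) method". The FAS requires randomisation and at least one dose; no post-baseline CIMT is needed. Significance is p ≤ 0.05, and no margin is mentioned.
- **Outcome measurement:** "Changes of the following outcomes from baseline (week 0) to endpoint (week 12) of intervention will be evaluated". The four-weekly visits under Safety outcomes are described for vital signs and symptoms; no CIMT scan between the two time points is described.
- **Drop-out criteria:** the list includes "Participants who fail to take the drugs as required or have incomplete data", as well as off-protocol drug changes, unblinding and unexplained loss to follow-up. Of these participants it says "They will be required to return for the last observation as much as possible", and their data are kept.
- **Sample size:** "The mean of CIMT of the placebo group is 1.12 mm" and "the mean of CIMT of the treatment group is estimated at 1.03 mm", with an SD of 0.10 in both groups. "The superiority margin is 0.03 (one-sided test, α = 0.025, 1-β = 0.8"). The minimum is 90, raised to 114 after "considering the dropout rate of 20" per cent.

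**The concern.** With one post-baseline time point, LOCF has no intermediate value to carry. For anyone without a later scan it becomes baseline carried forward, and the imputed zero enters the analysis with no allowance for its uncertainty. For anyone scanned on early exit, a shorter exposure stands in for twelve weeks.

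Two things are at stake. The first is power: dividing by 0.8 to reach 114 assumes that drop-outs leave the analysis, whereas the FAS with LOCF keeps them in, some of them with no treatment effect in their value. The second is bias: several drop-out reasons, such as adverse reactions, poor adherence, added drugs and unblinding, can plausibly differ by arm. If CIMT also changes under usual treatment, the arm with more dropout receives more zeros.

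**Working it through.** **Inputs.** From Sample size: difference 1.12 − 1.03 = 0.09 mm; margin 0.03 mm; SD 0.10; one-sided α 0.025; 45 per arm evaluable; 57 per arm enrolled. The article does not say whether 0.10 is the SD of week-12 values or of changes. Assumed here: the share q carried from baseline, the baseline to week-12 correlation r, and no mean change on placebo in step 2.

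**1. The plan's own figure.** Distance beyond the margin: 0.09 − 0.03 = 0.06. At 45 per arm, SE = 0.10 × √(2/45) = 0.0211 and 0.06/0.0211 = 2.85; the noncentral t gives 80.4% power (44 per arm gives 79.5%). So 90 reproduces. Then 45/0.8 = 56.25, rounded up to 57 per arm, or 114. With all 57 per arm observed, power would be 89%.

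**2. Equal dropout, share q carried from baseline in each arm.** The expected difference is 0.09 × (1 − q). At q = 0.20 it is 0.072, which is 0.042 beyond the margin. Mixing carried and observed values adds q(1 − q) × 0.09² to the SQXT-arm variance. Power = Φ(0.042/SE − 1.96), with SE = √[(V_SQXT + V_placebo)/57].

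- (a) Week-12 values, SD 0.10: V_SQXT = 0.01 + 0.16 × 0.0081 = 0.011296; V_placebo = 0.01; SE = 0.01933; 0.042/0.01933 = 2.17; power 58%.
- (b) SD of change 0.10 (the same as r = 0.5, since SD of change = 0.10 × √[2(1 − r)]), carried changes exactly 0: V_SQXT = 0.8 × 0.01 + 0.001296 = 0.009296; V_placebo = 0.008; SE = 0.01742; ratio 2.41; power 67%.
- (c) Change scores with r = 0.7, variance 0.006: V_SQXT = 0.0048 + 0.001296 = 0.006096; V_placebo = 0.0048; SE = 0.01383; ratio 3.04; power 86%.

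The same formulas at other values of q give power against the margin, 57 per arm:

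| q | (a) | (b) | (c) |
|---|---|---|---|
| 0 | 89% | 89% | 99% |
| 10% | 76% | 80% | 95% |
| 15% | 68% | 74% | 91% |
| 20% | 58% | 67% | 86% |

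Under (a) and (b), power stays at 80% until q reaches about 8% and 10% respectively. At q = 20%, 80% power would need 95 per arm under (a) and 77 under (b), that is 190 or 154 in total. A simulation of 40,000 trials gave 58% for (a) and 67% for (b) at q = 20%. An improvement shared by both arms would add to the mixture variance and lower these figures.

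Against zero instead of the margin, at q = 20%: 0.072/0.01933 = 3.72 under (a), power 96%; higher under (b) and (c).

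**3. Unequal dropout, no true effect (all assumed).** Both arms fall by 0.05 mm; 10% of SQXT and 30% of placebo are carried from baseline. Expected changes are 0.9 × 0.05 = 0.045 and 0.7 × 0.05 = 0.035, a spurious benefit of 0.010 mm.

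- r = 0.7: V_SQXT = 0.9 × 0.006 + 0.09 × 0.0025 = 0.005625; V_placebo = 0.7 × 0.006 + 0.21 × 0.0025 = 0.004725; SE = 0.01347; 0.010/0.01347 = 0.74; two-sided rejection against zero is about 11 to 12%.
- r = 0.5: variances 0.009225 and 0.007525; SE = 0.01714; ratio 0.58; about 9%.
- Against the 0.03 margin: (0.010 − 0.030)/SE is negative, and false claims of superiority occur in about 0.1% or fewer.

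Swapping the dropout rates reverses the sign. With the planned 0.09 mm effect and a 0.05 mm improvement on placebo, LOCF gives 0.9 × 0.14 − 0.7 × 0.05 = 0.091 mm with 10% SQXT and 30% placebo dropout, and 0.7 × 0.14 − 0.9 × 0.05 = 0.053 mm with the rates exchanged.

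**The case against.** The strongest reply is that the documents do not show how often baseline would be carried forward. Drop-outs are to be recalled for a last observation, and several listed reasons (poor adherence, added drugs, unblinding) describe people who may well still be scanned. If half of a 20% dropout return with the full effect retained, q is 10% and power under (a) or (b) is 76 to 80%. This stands. A reader might infer that drop-outs will mostly be scored as no change; the article does not support that.

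A reader might also infer that the trial simply fails to deliver 80% power. That does not follow either. The loss depends on q, on what the SD of 0.10 describes, and on testing against the margin. The primary outcome is a change, so the change-score readings are the more relevant ones, and at r = 0.7 power stays above 80% even with the full 20% carried forward.

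Nor may the lost power and the inflated error be added together. The 58 to 67% belongs to the margin test of the Sample size section; the 9 to 12% error belongs to a test against zero, where power is at least 96%. No single analysis has both problems at that size. The fall in both arms and the 10%/30% split are illustrative; the article gives neither.

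Finally, equal dropout biases toward no difference, which is conservative for superiority. The per-protocol set excludes drop-outs but is no unbiased substitute. Sensitivity analyses may sit in the analysis plan that is not shown, and their absence here is not counted. What remains is a rule the article itself fixes, and an enrolment figure that rests on a different handling of drop-outs.

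**Conclusion.** The point holds in conditional form. LOCF with a single post-baseline time point gives a change of exactly zero to anyone without a later scan, and a part-treatment value to anyone scanned early, both treated as observed. The sample size removes the 20% who drop out; the FAS keeps them. The two sections do not describe the same analysis.

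If all 20% are carried from baseline in both arms, the expected difference is 0.072 rather than 0.09 mm, and power against the margin lies between 58% and 86%, depending on the meaning of the SD and on r. That is the upper end of the problem, and it shrinks as more drop-outs return for a scan. The direction of bias is toward no difference with equal dropout and can go either way with unequal dropout and a change in both arms. A raised false-positive rate arises only in a test against zero, under assumed inputs.

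**What to change.** 1. In Data analysis, replace LOCF as the main FAS rule with a baseline-adjusted analysis of week-12 CIMT that is valid under missing at random: ANCOVA on observed data, or multiple imputation using at least arm and baseline CIMT. Add a reference-based sensitivity analysis and keep LOCF as a supplementary table only.
2. In Drop-out criteria, state that the last observation is the week-12 CIMT scan, to be sought from every randomised participant who has not withdrawn consent, whether or not study drug was stopped. This concerns data collection only; the listed reasons can stay as they are.

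The cost is an amendment to the analysis text, modest programming in the Stata version already named, effort to bring back drop-outs for a visit that is already scheduled, and slightly wider intervals. Recruitment was still under way at publication, so the change could be made before database lock and unblinding.

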#### Secondary objectives

This trial also aims to evaluate safety and explore therapeutic mechanism of SQXT formula in treating patients with diabetic peripheral atherosclerosis.

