#### Safety outcomes

Adverse event (AE) will be collected after the participants begin to receive drugs. The record of AE includes the following: descriptive analysis, time of occurrence and termination, severity, frequency of occurrence, whether treatment is needed, and if necessary, the treatment given needs recording.

Participants will be monitored for vital signs (body temperature, respiration, heart rate, BP) during the outpatient visit every 4 weeks, and will be asked for if they have any symptoms of discomfort.

Participants will have the following tests at the beginning and end of intervention: blood, urine and stool routine examination, electrocardiogram, liver function test (ALT, AST, TBIL, AKP, GGT), and renal function test (blood urea nitrogen, creatinine). Systemic symptoms of participants will be closely observed. If a participant has suspicious symptoms of respiratory system, circulatory system, liver or kidney disease, he will be immediately tested on safety.

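### The safety set admits only participants who had an adverse event, so adverse-event incidence in it is 100% in each arm by construction and cannot be compared

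*Protocol article*

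**What the plan says.** The protocol article defines its analysis sets in one paragraph under Data analysis. For safety it says: "The safety set (SS) includes participants who have been randomized to receive the drugs at least once and have experienced AE". The two conditions are joint: at least one dose, and an AE.

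The efficacy set in the same paragraph uses the same dosing condition with nothing added: "The Full Analysis Set (FAS) includes participants who have been randomized to receive the drugs at least once". The AE clause is thus the only difference between the two definitions.

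The next paragraph plans the comparison: "AE will be analyzed and described in detail, and the χ2 test will be used to compare the differences between groups if necessary". It does not name the analysis set for that test.

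Under Secondary objectives the article says: "This trial also aims to evaluate safety and explore therapeutic mechanism of SQXT formula". Under Safety outcomes, data collection carries no AE condition: "Adverse event (AE) will be collected after the participants begin to receive drugs", and for laboratory tests and ECG, "Participants will have the following tests at the beginning and end of intervention". No other section gives a different safety population or AE denominator.

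**The concern.** A safety population has to contain the treated patients who had no AE, because they form most of the denominator of any risk. Here they are removed. Three things follow.

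- Overall AE incidence carries no information: it is 100% in every arm that has an event.
- The frequency of a particular AE becomes a proportion among AE cases. If the formula raises AEs generally, numerator and denominator rise together and the excess largely cancels.
- Laboratory, ECG and vital-sign summaries in this set would omit the AE-free patients, although their data are collected. The remaining patients are selected on a post-randomisation event, so the comparison is no longer protected by randomisation.

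At stake is a stated objective of the trial: followed as written, the plan could report equal AE percentages in the two arms whatever the true difference in harm.

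**Working it through.** **Inputs from the article.** Planned enrolment is 114 with 1:1 allocation (Sample size), so 114 / 2 = 57 per arm. The 114 is consistent with the article's own inputs: 90 / (1 − 0.20) = 112.5, rounded up to 113, then to 114 for equal arms. The article states no AE rate and no safety power, so there is no safety figure to reproduce. All event counts below are assumptions, and every randomised participant is taken to have had at least one dose.

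**Step 1: incidence in the set as defined.** Let x be the number of treated participants in an arm with an AE, and n the number treated.

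- Risk among treated = x / n.
- Incidence in the safety set as defined = x / x = 100% for any x > 0, and 0/0 if x = 0.

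This holds for any counts and needs no assumption about rates.

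**Step 2: the chi-square test.** The table of arm by any AE has rows (x₁, 0) and (x₂, 0). The no-AE column total is 0, so the expected counts in that column are 0 and the Pearson statistic Σ(O − E)²/E is undefined.

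**Step 3: what is lost, over a range of assumed counts.** With 57 per arm and a Pearson chi-square without continuity correction, χ² = N(ad − bc)² / (product of the four margins):

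| AE cases (SQXT vs placebo) | Among all treated | Difference (points) | χ² | p | Safety set as defined |
|---|---|---|---|---|---|
| 6 vs 3 | 10.5% vs 5.3% | 5.3 | 1.09 | 0.30 | 6/6 vs 3/3, no test |
| 17 vs 6 | 29.8% vs 10.5% | 19.3 | 6.59 | 0.010 | 17/17 vs 6/6, no test |
| 23 vs 6 | 40.4% vs 10.5% | 29.8 | 13.37 | 0.0003 | 23/23 vs 6/6, no test |

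For the middle row: χ² = 114 × (17 × 51 − 40 × 6)² / (23 × 91 × 57 × 57) = 114 × 627² / 6,800,157 = 6.59. Fisher's exact test for the same row gives p = 0.018.

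**Step 4: a specific AE.** Suppose that, within the 17 versus 6 scenario, one type of AE occurs in 9 versus 3 patients.

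- Among treated: 9/57 = 15.8% versus 3/57 = 5.3%, a ratio of 3 (Fisher p = 0.12).
- In the safety set as defined: 9/17 = 53% versus 3/6 = 50%, a ratio of 1.06.

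A threefold difference in risk almost disappears. The comparison can be computed, but it no longer estimates a treatment effect on risk.

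**The case against.** The strongest points on the other side are these.

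- **The test's set is not named.** The chi-square sentence does not say that it will be run in the safety set, and it applies only if judged necessary. The full analysis set, as worded, is the treated denominator that is wanted. This stands as a limit: the comparison is impossible in the safety set, not in every set. But the safety set is the one designated for safety, and using it there is the natural reading.
- **No data are lost.** AEs are collected from first dose without an AE condition, and the number of cases per arm would still be visible. A reader who knew that about 57 per arm were randomised could rebuild approximate rates. This is true and softens any claim that harm would be entirely concealed. The reported percentages and the formal test would still be wrong.
- **It may be a slip of drafting or translation**, perhaps for treated participants with a safety record after dosing. That is plausible, but nothing in the article says so.
- **The full SAP is not shown.** The article says it was completed before the trial started, and it may define the set properly. But this is not a detail left to another document: the article states a definition, and that definition is wrong.
- **The example is chosen.** The 17 versus 6 scenario is significant with the correct denominator; 6 versus 3 is not (p = 0.30). That affects the illustration only. The 100% result does not depend on it.

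**Conclusion.** The concern holds. In the safety set as defined, any-AE incidence is 100% in every arm with an event, so it can be neither estimated nor compared. That conclusion rests only on the definition itself. Comparisons of specific AEs or of laboratory changes within the set are computable but condition on a post-randomisation outcome. The numerical loss depends on unknown AE rates: in the illustrated scenarios, true differences of 5.3 to 29.8 points all become zero. Because safety is a stated objective and this is the only population designated for it, the definition must be corrected. Efficacy analyses and data collection are unaffected.

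**What to change.** Delete the AE condition from the definition. State that the safety set is all randomised participants who took at least one dose, analysed by treatment received, and that it is the denominator for AE, laboratory, ECG and vital-sign summaries. Name this set in the sentence that plans the chi-square comparison.

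As an optional improvement, report the between-arm risk difference with an exact confidence interval. With small counts this is more informative than a test run only when thought necessary, but the error is repaired without it.

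The cost is one sentence in the protocol, plus the matching sentence in the SAP if it carries the same definition. No new data, visits or participants are needed, since the safety data are already collected without regard to AE status. The change should be documented before unblinding.

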**Methods:**

This is a randomized, double-blind, placebo-controlled add-on trial that is expected to enroll 114 diabetic patients with peripheral atherosclerosis. After a 2-week run-in period, participants will been randomly assigned in a 1:1 ratio and receive 12 weeks of usual treatment and SQXT formula (treatment group) or usual treatment and placebo (control group). The primary outcome is the change in carotid intima-media thickness from baseline to endpoint. The secondary outcomes are the structure and function of peripheral arteries, blood glucose and lipids, traditional Chinese medicine syndrome score, and quality of life, and safety and endpoint events are evaluated. To explore the therapeutic mechanism through oxidative stress, inflammation, and advanced glycation end products, and lipidomics will be used to screen for biomarkers for diagnosis and efficacy evaluation.

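### The tests listed for continuous outcomes do not adjust for baseline CIMT, and the sample size is worked on CIMT levels although the outcome is change, so the 80% power rests on an unstated correlation

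*Protocol article*

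**What the plan says.** The Abstract of the protocol article defines the outcome: "The primary outcome is the change in carotid intima-media thickness from baseline to endpoint". The Outcome measurement section applies the same definition to all efficacy outcomes: "Changes of the following outcomes from baseline (week 0) to endpoint (week 12) of intervention will be evaluated". Week-0 CIMT is therefore collected on every participant who contributes to the primary outcome.

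The Sample size section works with group means of CIMT itself. For control, "The mean of CIMT of the placebo group is 1.12 mm"; for the active arm, "the mean of CIMT of the treatment group is estimated at 1.03 mm". The spread is given beside them: "the standard deviation of two groups is 0.10". The other inputs are a superiority margin of 0.03, a one-sided α of 0.025, power of 0.8 and 1:1 allocation. These lead to a minimum of 90 participants, raised to 114 for 20% dropout. No SD of change and no correlation between visits is given.

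The Data analysis section gives one general list of between-group tests: "Difference between groups will be assessed with t-test, analysis of variance (ANOVA), rank sum test, and chi-square". It assigns none of them to CIMT by name. For the clinical endpoint events it adds Cox regression on prognostic factors, but it names no covariate model for the continuous outcomes. It also says of a separate document, not shown here, "The statistical analysis plan is completed and confirmed before the start of trial".

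**The concern.** Two things do not fit together well.

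First, the outcome is a within-person change, while the sample size uses means of levels and an SD stated with them. The SD of a change depends on how strongly the week-0 and week-12 readings correlate. Power computed with the SD of levels carries over to the change score at only one value of that correlation.

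Second, the listed tests for continuous outcomes make no use of baseline as a covariate. With two arms, one-way ANOVA is the t-test (F = t²). With two time points, the group-by-time test of a repeated-measures ANOVA is the t-test on change. The presence of ANOVA in the list therefore adds no baseline adjustment.

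At stake are the precision of the primary comparison, and of the other continuous outcomes if they are handled the same way, and whether the stated power describes the analysis that will be done.

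**Working it through.** **Inputs from the Sample size section.** Means 1.12 and 1.03 mm; SD 0.10; margin 0.03; one-sided α 0.025; power 0.80; ratio 1:1; minimum total 90; dropout 20%; enrolled total 114.

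**Assumptions, not in the documents.** The SD of 0.10 is the SD of CIMT levels and is the same at week 0 and week 12. The correlation r between the two readings is unknown, so a range is shown.

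**Step 1: reproduce the plan's figure.**
- Difference beyond the margin: (1.12 − 1.03) − 0.03 = 0.06 mm.
- Normal approximation: n per arm = 2 × (1.960 + 0.842)² × 0.10² / 0.06² = 43.6, so 44 per arm and 88 in total.
- Noncentral t: 45 per arm, 90 in total, power 80.4%. This matches the stated 90.
- Dropout: 45 / 0.8 = 56.25, so 57 per arm and 114 in total. This matches the stated 114.

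The stated numbers are therefore those of an unadjusted two-sample t-test with an SD of 0.10.

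**Step 2: move to the declared outcome.**
- SD of change = 0.10 × √(2(1 − r)). It equals 0.10 only when r = 0.5.
- Residual SD under ANCOVA = 0.10 × √(1 − r²).
- Ratio of variances, ANCOVA to change score = (1 − r²) / (2(1 − r)) = (1 + r)/2, which never exceeds 1.

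**Step 3: power at 45 per arm for 0.06 mm, noncentral t.**

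| r (assumed) | SD of change | Power, t-test on change | ANCOVA SD | Power, ANCOVA | Variance ratio |
|---|---|---|---|---|---|
| 0 | 0.141 | 51% | 0.100 | 80% | 0.50 |
| 0.3 | 0.118 | 66% | 0.095 | 84% | 0.65 |
| 0.5 | 0.100 | 80% | 0.087 | 90% | 0.75 |
| 0.7 | 0.077 | 95% | 0.071 | 98% | 0.85 |
| 0.8 | 0.063 | 99% | 0.060 | >99% | 0.90 |

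**Step 4: the same in sample size.** Evaluable totals for 80% power (normal approximation), change score then ANCOVA: 124 and 80 at r = 0.3; 88 and 66 at r = 0.5; 54 and 46 at r = 0.7.

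**Step 5: sensitivity to the assumptions.**
- Unequal SDs: with an illustrative baseline SD of 0.08 and a week-12 SD of 0.10, the SD of change at r = 0.4 is √(0.08² + 0.10² − 2 × 0.4 × 0.08 × 0.10) = 0.100. Change-score power then reaches 80% at r = 0.4 rather than 0.5.
- Number analysed: if all 57 per arm enter the full analysis set with the same effect and SD, change-score power is about 77% at r = 0.3 and 83% at r = 0.4. Values carried forward from dropouts could dilute the effect and offset part of this gain.

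**The case against.** The strongest reply is that the Data analysis section is a generic list in a condensed article. It ties no test to CIMT, and the separate analysis plan may already specify a baseline-adjusted model. This stands as far as it goes: a reader might infer that the primary analysis is fixed as an unadjusted t-test or rank test, and the article does not say so. It does not remove the point, because the tests that the article states for continuous outcomes are all unadjusted and a better method is available from data already collected. If the analysis plan specifies ANCOVA, the published list should be aligned with it.

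Other stronger readings also fail:

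- *Baseline is thrown away.* A change score subtracts baseline. It does not use it as a covariate, which costs efficiency but leaves the test valid and unbiased under randomisation.
- *The trial is underpowered.* On equal SDs, power falls below 80% only if r is under 0.5. The article gives no r, and its Discussion counts repeatable measurement among the advantages of the vascular tests. Above 0.5 the sample size is conservative, and at r = 0.7 ANCOVA adds only about 2 percentage points (95.3% to 97.6%).
- *Baseline imbalance is likely.* Nothing in the article supports that. That it mentions no stratification is not evidence of it.
- *The test will be chosen after a normality check.* The article links normality to how data are described. It states no such rule for choosing tests.

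**Conclusion.** The point holds as an improvement available at no cost, not as an error in the plan. The stated 90 and 114 are arithmetically correct for what was calculated. What holds is that the listed tests for continuous outcomes make no baseline adjustment, and that the power calculation is on levels while the outcome is change. The stated 80% therefore carries over to a change-score test only at r = 0.5, given that 0.10 is the SD of levels and is equal at both visits.

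The size of the gain depends on r, which is assumed throughout. At 45 per arm ANCOVA adds about 18 percentage points of power at r = 0.3, 10 at r = 0.5 and 2 at r = 0.7. Its practical merit is that it holds at about 80% or more for any r from 0 upwards, so the power no longer depends on an unknown ultrasound correlation. No power shortfall is demonstrated.

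**What to change.** 1. Data analysis: make the primary analysis an ANCOVA of week-12 CIMT on treatment arm with baseline CIMT as covariate. Report the adjusted difference with its 95% confidence interval and read that interval against the 0.03 margin. The limit on the margin side corresponds to the one-sided 0.025 level used for the sample size.
2. Use the same model for the other continuous outcomes, each with its own baseline value, and keep the unadjusted test as a sensitivity analysis.
3. Sample size: state whether 0.10 is the SD of CIMT levels or of change, and which baseline-to-week-12 correlation is assumed. If the correlation is unknown, show power over a range.

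If the separate analysis plan already contains such a model, the change reduces to aligning the published text with it. The cost is wording only: week-0 CIMT is already measured, and no new data or patients are needed. Because recruitment is under way, the change should be made and dated before unblinding.
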